Differences in androgen receptor (AR) activity and hence sensitivity to androgens might complicate the relationship between androgens and sexual function. Functional studies have demonstrated that an inverse relationship exists between the CAG repeat length and receptor expression impacting on the strength of the androgen action and sensitivity to sex hormones.^72^ Several authors have studied the potential association between shorter CAG repeats and a high testosterone level in PCOS as well as the general population, with conflicting results.^73^, ^74^, ^75^, ^76^, ^77^, ^78^, ^79^ Ethnicity, small sample sizes, and different definitions of PCOS and hyperandrogenism may underlie these inconsistent results. Moreover, a non-linear relationship between CAG length and AR activity has been suggested.^80^ Therefore, it is plausible that CAG repeat length variants are involved in the pathogenesis of women with hyperandrogenism and influence sexual function. For instance, a recent Danish population study showed that lower numbers of CAG repeats were associated with problems in reaching orgasm.^81^

The impact of OCP use on endocrine and sexual function has been studied extensively in healthy women.^82^, ^83^, ^84^, ^85^, ^86^, ^87^, ^88^, ^89^, ^90^, ^91^, ^92^ OCPs are known to decrease androgen and free testosterone levels.^56^^,^^57^^,^^90^^,^^92^ Hypothetically, sexual function can be influenced by this mechanism. Repeatedly, studies have shown that some women report an OCP-related improvement in sexual function, some a deterioration, whereas many report no change in sexual function.^82^, ^83^, ^84^, ^85^, ^86^^,^^88^^,^^89^^,^^93^ In women with PCOS, OCPs can restore androgen levels to normal, improving clinical symptoms like acne and to a lesser extent hirsutism.^7^ Few studies have assessed its influence on sexual function. Results varied from improvement of sexual function, while normalizing androgen levels,^94^ to deterioration of sexual desire.^95^

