We expect to find lower sexual function and higher sexual distress in the PCOS group compared with the control group.^38^ Further, we expect to find stronger genital and self-reported sexual responsiveness in women with higher androgen levels in both the fantasy and vibrotactile stimulation conditions but not with visual sexual stimuli.^99^^,^^100^

Following the threshold model,^64^, ^65^, ^66^, ^67^, ^68^, ^69^, ^70^, ^71^ we do not predict a linear relationship between VPA response and androgen levels (free testosterone and total testosterone). We do expect women with the lowest bioavailable androgen levels (control women using OCPs) to show lower levels of VPA response than women in the upper 3 quartiles of bioavailable androgen levels (women with PCOS not using OCPs).

We hypothesize that women with PCOS will score lower on various psychosocial and mental health measures compared with control women.^17^ We expect these scores to be associated with impaired scores on sexual function questionnaires.^34^, ^35^, ^36^, ^37^

We have no specific expectation for the relationship between sexual outcomes and CAG repeat length in both women with and without PCOS. CAG repeat length will be measured to exploratively assess individual differences in sensitivity to androgens and the relationship with PCOS status and other variables.

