## Methods

### Design

This study is a non-randomized observational prospective case control study in a multicenter setting assessing the difference in sexual function between women with and without PCOS. Additionally, we examine the effect of OCP use resulting in a 2×2 design. The duration of the study will be 4 years. 3 Dutch academic medical centers will participate in this study: Erasmus Medical Center Rotterdam, Leiden University Medical Center (LUMC), and Amsterdam University Medical Center (AMC). Independent variables are PCOS status and OCP use. The dependent variables are sexual function as assessed with questionnaires and genital and self-reported sexual arousal in a laboratory setting.

Ethical approval was awarded by the Ethics Committee of Erasmus Medical Center, Rotterdam, The Netherlands (MEC 2016-216, NL55484.078.16). Local ethical approval was awarded by the Ethics Committees of LUMC (P16.299) and AMC (2016_182/NL55484.078.16).

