### Participant Recruitment and Selection

Women who have been diagnosed with PCOS at the outpatient clinic of the Erasmus University Medical Center will be asked to participate in this study. Also, Dutch patient societies will be requested to advertise for our study. PCOS will be diagnosed according to the Rotterdam criteria.

An age-matched control group of healthy women will be recruited through advertisements in local newspapers, social media, or flyers at the outpatient gynecological clinics of Erasmus University Medical Center, LUMC, and AMC. Control women will also be recruited through the pool of volunteers available at LUMC. In the control group, women with PCOS will be excluded. In case PCOS is diagnosed, data will be used in the PCOS arm.

Inclusion criteria for participation are healthy women with a diagnosis of PCOS, healthy women without another diagnosis concerning the menstrual cycle, women aged between 18 and 40 years, and those with a stable heterosexual relationship for at least 6 months. Due to the nature of the erotic film material and the sexuality questionnaires, only heterosexual women are eligible.

Medical screening involves endocrine screening, assessment of BMI, a menstrual cycle history, a modified Ferriman-Gallwey score, and a transvaginal ultrasound in order to assess the ovarian morphology, antral follicle counts, and ovarian volumes of both ovaries. Total endometrial thickness will also be recorded as well as uterine sizes. The diagnosis of PCOS or of a normal menstrual cycle will be made after a standardized initial examination is performed between 07:45 and 10:00 am after an overnight fast in the early follicular phase of the menstrual cycle (third to fifth day of menses when no hormonal contraception is used) in case of a regular menstrual cycle. In case of a cycle irregularity, the examination will be performed on a random cycle day. In case of OCP use, screening will be on the eighth day of a new cycle after 7 days of not using OCPs. Endocrine features combined with medical screening will determine the diagnosis.

We will recruit women with PCOS and healthy women both either not using hormonal contraceptives (for at least 3 months prior to the start of their participation in this research project) or using OCPs for at least 3 months. We aim to include a similar number of women using OCPs as women not on OCPs in both the PCOS group and the control group.

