### Materials and Measures

#### Blood Samples and Endocrine Screening

Peripheral venous blood samples to assess androgen levels will be collected in all participants: total testosterone, SHBG, and calculated free androgen index: testosterone × 100/SHBG. Additionally, all of the following will be assessed in all participants: estradiol, progesterone, luteinizing hormone, follicle stimulating hormone, androstedione, dehydroepiandrosterone, dehydroepiandrosterone sulfate, thyroid stimulating hormone, prolactin, lipids, and fasting glucose and insulin. Plasma will be stored at −80°C. Samples will be analyzed using liquid chromatography mass spectrometry.

We will determine the number of CAG repeats in 4 different ways: the number of CAG repeats in the allele containing the fewest CAG repeats (short allele), the number of CAG repeats in the allele containing the most CAG repeats (long allele), the mean number of CAG repeats (biallelic mean), and the number of CAG repeats in the active X chromosome based on X-inactivation analysis (X-weighted biallelic mean). The CAG repeat region in the first exon of the AR gene on the X chromosome will be amplified from genomic DNA with a polymerase chain reaction-based assay. Another possibility is to define single nucleotide polymorphisms that will detect the different variable number tandem repeat alleles and perform a less cumbersome Global Screening Array. We probably will take the latter approach to determine AR sensitivity.

The medical and endocrine screening as well as the DNA analysis for all participants will be done at 1 laboratory at Erasmus University Medical Center, to ensure compatibility of data.

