### Statistical Analysis

Normality of the outcome data will be determined with Shapiro-Wilk tests. In case of non-normality, an appropriate transformation will be performed. The difference between women with PCOS and controls will be analyzed with separate multilevel regression analyses for each of the 5 outcomes. Independent variables will be PCOS (vs controls), fantasy (vs film), and vibration and interactions of PCOS with fantasy and vibration. *P* values of .01 will be considered significant.

For the differences between women with PCOS and controls, and women using OCPs and women not using OCPs, OCP use and interactions with PCOS, fantasy, and vibration will be added to the multilevel analyses.

Mediation regression analyses, as described by Mathieu and Tailor,^129^ will be extended to multilevel mediation regression analyses to estimate the mediating effects of steroid hormone levels, and sexual and psychosocial parameters in the relation of PCOS/OCP use on the 5 sexual outcome measures.

We will apply regression curve estimation with sexual function as the dependent variable and CAG repeat length and several functions of the CAG repeat length as independent variables to analyze a possible non-linear relation.

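### The exploratory CAG-repeat regression has no term for ethnicity, although the Background says ethnicity may explain inconsistent CAG findings; confounding cannot be excluded, and an adjustment would be cheap.

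*Protocol article*

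**What the plan says.** All references are to the protocol article.

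- **Background.** Earlier studies looked at the "potential association between shorter CAG repeats and a high testosterone level in PCOS as well as the general population, with conflicting results". The authors then comment: "Ethnicity, small sample sizes, and different definitions of PCOS and hyperandrogenism may underlie these inconsistent results".
- **Background, on the status of the aim.** "CAG repeat length will be measured to exploratively assess individual differences in sensitivity to androgens". The authors state no directional expectation.
- **Participant Recruitment and Selection.** "Medical screening involves endocrine screening, assessment of BMI, a menstrual cycle history, a modified Ferriman-Gallwey score, and a transvaginal ultrasound". On controls: "An age-matched control group of healthy women will be recruited through advertisements in local newspapers, social media, or flyers". Eligibility sets no ethnic restriction, and age is the only matching variable named.
- **Design and Table 1.** "Independent variables are PCOS status and OCP use". Neither the questionnaires nor the moderators include ethnicity.
- **Blood Samples and Endocrine Screening.** CAG length is to be scored in four ways. The probable laboratory route is to "perform a less cumbersome Global Screening Array", and ancestry adjustment is not mentioned.
- **Statistical Analysis.** The CAG model is fitted "with sexual function as the dependent variable and CAG repeat length and several functions of the CAG repeat length as independent variables", in order to look for non-linearity.

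**The concern.** In a genetic association analysis, a group structure linked to both genotype and outcome can produce an association without any effect of the genotype. Adjusting for ethnicity or ancestry is the standard protection. Here the authors raise ethnicity themselves as a possible reason why CAG findings disagree. They then state the predictors of their own CAG model, and ethnicity is not among them. Design does not remove the problem either, because neither eligibility nor matching addresses ethnicity.

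What is at stake is how an exploratory result can be read. The abstract counts the DNA analysis among the study's strengths, and the Discussion expects exploratory associations to generate hypotheses for later studies. A CAG signal from an unadjusted model would leave open whether it reflects androgen sensitivity or the ethnic mix of the sample.

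**Working it through.** **1. The plan's own figure.** The article gives no figure for the CAG analysis, so there is none to reproduce on this point. The sample size is needed only as an input. For d = 0.60, two-sided alpha 0.01 and power 0.80, a t-test calculation gives 66.6, so 67 per group and 134 in total, as stated. With 10% dropout, 134/0.90 = 148.9, or 75 per group, which gives the stated 150. The point leaves these figures unchanged.

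**2. What confounding would require.** Two links are needed:

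| Link | What the article says |
|---|---|
| Ethnicity and CAG length | Not stated directly. Ethnicity is named as a possible reason for conflicting CAG–testosterone results. |
| Ethnicity and sexual function | Not stated anywhere. |

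The article therefore makes confounding possible but does not establish it.

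**3. How large it could be.** Every input except n = 134 is an assumption, because the article gives no ethnic mix and no group differences. Let a share p of the women belong to a second group whose mean CAG length differs by d1 within-group SDs and whose mean sexual-function score differs by d2. There is no true CAG effect within groups. With v = p(1 − p), the pooled correlation is

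r = v·d1·d2 / √[(1 + v·d1²)(1 + v·d2²)]

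A two-sided test of r uses z = arctanh(r)·√(n − 3) = arctanh(r)·√131. The chance of a significant result is Φ(z − c) + Φ(−z − c), with c = 1.960 at 0.05 and c = 2.576 at 0.01.

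Worked example with p = 0.3, d1 = 0.8, d2 = 0.5:
- v = 0.21
- r = 0.084/√(1.1344 × 1.0525) = 0.077
- z = 0.88
- false-positive rate 14.3% at 0.05 and 4.5% at 0.01

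| p | d1 | d2 | Spurious r | Rate at 0.05 | Rate at 0.01 |
|---|---|---|---|---|---|
| any | any | 0 | 0 | 5.0% | 1.0% |
| 0.1 | 0.3 | 0.2 | 0.005 | 5.0% | 1.0% |
| 0.2 | 0.4 | 0.3 | 0.019 | 5.5% | 1.2% |
| 0.2 | 0.8 | 0.3 | 0.036 | 7.0% | 1.7% |
| 0.3 | 0.8 | 0.5 | 0.077 | 14.3% | 4.5% |
| 0.4 | 1.0 | 0.5 | 0.105 | 22.5% | 8.5% |

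A simulation with 134 women and 20,000 replicates per scenario agrees for three of these rows. It gave 5.6% at 0.05 for the third row, 14% and 4% for the fifth, and 22% and 9% for the last.

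Even in the last row the spurious association explains only 0.105² ≈ 1.1% of the variance. The rates are for one linear test. The article plans several functions of CAG length and four ways of scoring it, and that multiplicity is not modelled here.

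**4. An indirect route through PCOS status.** The authors expect lower sexual function in women with PCOS, and the CAG model names no PCOS term. If the ethnic mix differed between the groups, ethnicity would be related to the outcome even without a direct effect. Assume minority shares of 35% in the PCOS group and 15% in controls, equal group sizes and a PCOS effect of 0.6 SD:
- PCOS makes up 0.35/0.50 = 70% of the minority women and 0.65/1.50 = 43.3% of the others.
- d2 = (0.700 − 0.433) × 0.6 = 0.16.
- With p = 0.25 and d1 = 0.8, r = 0.023, with rates of 5.8% at 0.05 and 1.3% at 0.01.

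On its own this route is small.

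**The case against.** **The article is condensed.** Its lists of measures are not exhaustive: age is both an eligibility criterion and the matching variable, yet it appears in neither the screening list nor Table 1. Ethnicity may well be recorded, and covariate sets are often left to the full protocol or analysis plan. This stands as far as data collection goes: the article does not show that ethnicity goes unrecorded. It does not dispose of the model, whose predictors are stated without ethnicity.

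**The Background remark is about something else.** It concerns CAG length and testosterone and says only that ethnicity may contribute, next to small samples and differing definitions. That fits differences between studies as well as confounding within one. This stands. A reader might infer that the authors identified a confounder and let that same confounding into their own result. The text does not support this, since no passage links ethnicity to sexual function.

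**The aim is exploratory.** This also stands. The CAG analysis is not one of the five primary comparisons, and the article does not claim that it will settle the question.

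**Recruitment.** A reader might infer that cases and controls come from different cities and so differ in ethnic mix. The article does not show this: flyers for controls are also placed at Erasmus, and PCOS women come partly through national patient societies. The recruitment channels do differ, but any difference in ethnic mix is conjecture.

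**Non-linearity.** A reader might also infer that a mixture of groups would mimic the curve being sought. The calculation here covers a linear association only, so no such claim is made.

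**Conclusion.** The point holds as a cheap improvement. The CAG model as written contains only repeat length and functions of it. The article itself mentions ethnicity as a possible reason for inconsistent CAG findings, and lists no ethnicity measure. Confounding of the CAG–sexual function association by ethnicity therefore cannot be excluded.

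Its size is unknown. It is nil if sexual function does not differ by ethnicity. Under the assumed differences, spurious r reaches at most about 0.10, with a false-positive rate between nominal and about 8.5% at 0.01, or 22% at 0.05. The top of that range needs 40% of the women to differ by a full SD in CAG length and half an SD in score, which nothing in the article supports or rules out. The primary comparisons and the sample size are unaffected.

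**What to change.** 1. If ethnicity is not already collected, add one self-report item to the existing online questionnaire, and send it to women already enrolled.
2. If the genome-wide array is run, ancestry components from it can serve instead or as well. The article calls this route only probable, so the questionnaire item is the safer basis.
3. Add ethnicity or ancestry as a covariate in every CAG model, and report the CAG estimates with and without it.

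The cost is a few degrees of freedom, at most one questionnaire item and a short amendment. If ethnicity is already recorded, only the model statement needs to change.

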In addition to differences in androgen sensitivity, in women with PCOS neuronal circuits in the brain might be impaired due to hyperandrogenism, resulting in a disruption of sex steroid feedback mechanisms.^96^^,^^97^ Following this line of reasoning, we will assess androgen levels, CAG repeat length, and actual genital response to sexual stimuli (vibrotactile, film fantasy) in a psychophysiological laboratory setting while taking into account the other factors presented here. As a result, we hope to be able to shed more light on the role of androgen levels in sexual responsiveness of women with PCOS.

Women with PCOS report significantly less sexual arousal and lubrication compared to normal controls,^38^ but it is unknown whether women with PCOS actually show abnormal physiological sexual responses. A pilot study concerning the effect of circulating androgen levels found no significant differences in clitoral vascularization in non-aroused women with PCOS in comparison with control women,^98^ but nothing is known about the genital response to sexual stimulation. There are indications that androgens influence sexual response to sexual fantasies and genital tactile stimulation, whereas the effect of visual stimuli is less influenced by androgen levels.^99^^,^^100^ To objectively assess genital response to sexual stimuli and its contribution to sexual function, psychophysiological measurements with vaginal pulse amplitude (VPA) are required.

The primary aim of this study is to assess differences between women with PCOS and control women in the following sexual outcome measures: Female Sexual Function Index (FSFI), Female Sexual Distress Scale-Revised (FSDS-R), Sexual Desire Inventory (SDI), and genital and subjective sexual responsiveness to sexual stimuli measured with VPA. Secondary aims are to investigate differences in these outcome measures between OCP users and non-users in interaction with PCOS status in an exploratory way, and to assess factors that may mediate the relationship between PCOS status and sexual outcome measures.

We will assess the following mediators: testosterone, free androgen levels, OCP use, sensitivity to androgens (using CAG repeat length), body mass index (BMI), body image, mental health, and self-esteem.

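### The planned curve fit on CAG repeat length can show an association with sexual function but cannot isolate a difference in sensitivity to androgens

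*Protocol article*

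**What the plan says.** **Purpose.** The Background introduces the receptor gene with this reason: "Differences in androgen receptor (AR) activity and hence sensitivity to androgens might complicate the relationship between androgens and sexual function". Among the hypotheses it adds: "CAG repeat length will be measured to exploratively assess individual differences in sensitivity to androgens and the relationship with PCOS status and other variables". No direction is predicted: "We have no specific expectation for the relationship between sexual outcomes and CAG repeat length in both women with and without PCOS".

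**Analysis.** The last paragraph of Statistical Analysis takes sexual function as the dependent variable and, on the other side, "CAG repeat length and several functions of the CAG repeat length as independent variables to analyze a possible non-linear relation". It names no androgen level and no CAG-by-androgen term.

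**Data.** Blood Samples and Endocrine Screening provides "total testosterone, SHBG, and calculated free androgen index" for every participant, so the androgen variables for such a term are already collected.

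**Second role.** The Abstract (Main outcome measures) and the end of the aims in the Background list CAG-based sensitivity among the mediators, next to testosterone and free androgen levels. The mediation paragraph of Statistical Analysis is meant "to estimate the mediating effects of steroid hormone levels, and sexual and psychosocial parameters in the relation of PCOS/OCP use" and does not name CAG. The Questionnaires section explains that some variables are treated as moderators because PCOS status does not cause them.

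**The concern.** Receptor sensitivity that complicates the relation between androgens and sexual function is effect modification: the same androgen level has a stronger or weaker effect according to repeat length. Estimating it needs the androgen level, the CAG length and their product in one model. The stated model has only CAG length, so it compares average sexual function between women with different repeat lengths, whatever their androgen levels.

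What is at stake is interpretation, in both directions. A flat curve is compatible with a real sensitivity difference, and a clear curve is compatible with none. The 2×2 design (PCOS by OCP use) is expected to spread androgen levels, with control women on OCPs lowest, so the data suit the question that this model leaves out.

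The mediator label does not close the gap. A mediator lies on the path from PCOS or OCP use to the outcome, and mediation analysis is not a test of effect modification. CAG length is read from genomic DNA, and the Background itself suggests that repeat variants may contribute to the origin of hyperandrogenism, which puts CAG before PCOS. By the article's own rule it belongs with the moderators.

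**Working it through.** **1. The plan's own figure.** The article gives no figure for the CAG analysis. Its sample size supplies the N. For the SDI, d = 0.60, two-sided alpha 0.01 and power 0.80:

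- Normal approximation: n = 2(2.576 + 0.842)² / 0.60² = 64.9, so 65 per group.
- Exact t test: n = 66.6, so 67 per group, as stated; 2 × 67 = 134.
- Dropout: 67 / 0.90 = 74.4, so 75 per group and 150 in total, as stated.

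The sample size reproduces and is not in question. N = 134 is used below.

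**2. What the curve estimates.** Let A be androgen level in SD units, measured from the level at which CAG length makes no difference through sensitivity, with mean m. Let S be standardised CAG length, independent of A. Write

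Y = a·A + c·S + b·A·S + error

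Here b is the sensitivity difference and c is a direct CAG effect. Averaging over A at a given S:

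E(Y | S) = a·m + (c + b·m)·S

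The curve on CAG sees only the sum c + b·m:

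- b = −0.3, c = 0, m = 0: slope 0. There is a sensitivity difference and the mean curve is flat.
- b = −0.3, c = 0, m = 1: slope −0.3.
- b = 0, c = −0.3: slope −0.3. There is no sensitivity difference, and the mean curve is the same as in the line above.

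No sample size separates the last two from the mean curve on CAG alone.

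**3. Size by simulation.** Assumptions, since the documents give no slopes: N = 134, residual SD 1, A and S normal and independent, b or c = −0.3, androgen main slope 0.2 to 0.3. The article does not say which functions of CAG length it will use, so a quadratic curve (2-df F test) and a cubic curve (3-df F test) were both tried. Entries are the share of studies significant at 0.05; the cubic runs show 0.01 in brackets.

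| Truth | Quadratic curve | Product term | Cubic curve | Product term |
|---|---|---|---|---|
| Sensitivity only, m = 0 | 8% | 88% | 10% (3%) | 91% (74%) |
| Sensitivity only, m = 1 SD | 83% | 89% | 76% (55%) | 90% (75%) |
| Sensitivity only, m = 2 SD | 100% | 89% | 100% (100%) | 90% (76%) |
| Direct CAG effect only | 85% | 5% | 79% (57%) | 5% (1%) |

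The curve's result for the same sensitivity difference runs from near chance to certainty as m changes. It is also significant in most studies with no sensitivity difference. The product term stays near 90% in the first three rows and at its nominal level in the fourth.

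**4. A smaller effect.** With b = 0.1 the product term is significant in about 20% of studies at 0.05 and 7% at 0.01.

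**The case against.** Four points on the other side have weight.

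*The curve is not blind to sensitivity.* A reader might infer that the planned model cannot detect a sensitivity difference at all. That holds only when the average woman sits at the point of no effect (m = 0), the least favourable case for the curve. Serum androgens are positive, and a receptor effect should vanish at zero androgen, so m may well exceed 0; at m = 2 SD the curve is the more powerful test. The documents do not give m. This stands: the defect is failure to isolate, not failure to detect.

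*The curve answers a question the article asks.* The Background speaks of the relationship between sexual outcomes and CAG length, cites a population study linking fewer repeats to problems in reaching orgasm, and mentions a suggested non-linear relation between CAG length and receptor activity. No CAG-by-androgen hypothesis is stated. This also stands, so replacing the curve is not justified. It does not meet the other stated aim: "CAG repeat length will be measured to exploratively assess individual differences in sensitivity to androgens".

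*The assumed effects are large.* With an androgen slope of 0.2 and b = −0.3, the slope changes sign for S above 0.2 / 0.3 = 0.67, about 25% of women. With b = 0.1 the added term would usually return a null as well. This limits what the fix can deliver, but it does not make the curve a measure of sensitivity.

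*The article is condensed and the analysis is exploratory.* A full analysis plan could contain the product term, and nothing in the article says that a flat curve would be read as absence of a sensitivity difference. Both are fair and lower the priority. The point does not rest on missing detail, however: the article states the predictors of its CAG model, and they do not match the stated purpose.

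**Conclusion.** The point holds in this form: the stated CAG model tests a CAG-outcome association and cannot isolate a difference in androgen sensitivity. The algebra in step 2 needs no assumed effect size, only the additive model with A and S independent. The percentages rest on assumed slopes of 0.3 SD, normal variables and 134 women: about 8% to 100% significant curves for the same sensitivity difference, and about 85% (79% with a cubic) for a direct effect alone. Independence of CAG length and androgen level is itself an assumption, since the Background reports conflicting findings on that association.

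The documents do not support reading this as a failed analysis or as a threat to the main results. No primary comparison, sample size or confirmatory test depends on it. It is worth correcting because the purpose and the model disagree, and the correction is nearly free.

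**What to change.** 1. Keep the curve fit, and describe it as a test of association between CAG length and sexual function.
2. Add one exploratory model with log free androgen index, CAG length, their product, PCOS status and OCP use. Read the product term as the estimate of androgen sensitivity and report it with a confidence interval. Centre both variables, and say beforehand which of the four CAG summaries enters.
3. Reconcile the mediator label for CAG in the Abstract and Background with the moderator rule in Questionnaires and with the mediation paragraph, which omits CAG.

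The cost is wording in the analysis plan; every variable is already measured. The drawback is imprecision: at 134 women a product term of 0.1 has about 20% power at 0.05. The model should therefore stay labelled exploratory, with a statement that a null product term is not evidence of no sensitivity difference.
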